# Lapatinib-capecitabine versus capecitabine alone as radiosensitizers in RAS wild-type resectable rectal cancer, an adaptive randomized phase II trial (LaRRC trial): study protocol for a randomized controlled trial

**DOI:** 10.1186/s13063-016-1583-y

**Published:** 2016-09-21

**Keywords:** Rectal neoplasms, Radiotherapy, Capecitabine (capecitabine [supplementary concept]), Lapatinib (lapatinib [supplementary concept]), Neoadjuvant therapy, Clinical trial, Phase II, Randomized adaptive trial, Bayesian adaptive randomization

## Abstract

**Background:**

Preoperative radiochemotherapy followed by surgical removal of the rectum with total mesorectum excision is the preferred treatment option for stages II and III rectal cancer. However, development of metastatic disease is the main cause of death for these patients with 5-year disease-free survival rates of 56 %. Anti-epidermal growth factor receptor (EGFR) targeted therapy is effective in metastatic rectal cancer, and human epidermal growth factor receptor 2 (HER-2) signaling may mediate resistance to EGFR inhibitors. Moreover, preclinical data support a synergistic effect of EGFR inhibition with radiation therapy.

**Methods/design:**

This Bayesian phase II trial with adaptive randomization was designed to assess the efficacy of adding lapatinib, a dual inhibitor of EGFR and HER-2, to standard radiochemotherapy with capecitabine in stages II and III rectal cancer.

**Discussion:**

The results of this trial will provide evidence of the feasibility and efficacy of the combination of lapatinib-capecitabine as radiosensitizers and explore potential predictive biomarkers for response to this novel neoadjuvant approach to resectable rectal cancer.

**Trial registration:**

EudraCT 2013-001203-36. Registered on 13 December 2013.

## Background

Colorectal cancer is the third most incident cancer and the second most common cause of cancer death in Europe [1]. Cancer of the rectum accounts for a third of colorectal cancer cases [2] with 5-year survival rates ranging from 28–55 % in men and 30–64 % in women [3].

Current treatment options for patients with rectal cancer include surgery, radiation therapy, chemotherapy, and targeted systemic therapy. The choice of therapy depends on disease stage, overall health status, and patient preferences. For localized disease, surgical removal of the rectum with total mesorectum excision is the surgical technique of choice, with an estimated overall survival of 86 % and a local recurrence rate of 9 % at 2 years [4]. However, the use of radiotherapy before surgical resection decreases local recurrence rate and impacts overall survival [5]. Moreover, the addition of fluoropyrimidine-based chemotherapy to preoperative radiotherapy further improves local control and pathologic response rates [6]. In patients treated with preoperative radiochemotherapy, whenever downstaging occurs, the risk of death due to cancer is significantly reduced [7]. Despite these therapeutic improvements, patients with localized rectal cancer have 5-year disease-free and overall survival rates of about 59 % and 67 %, respectively [8, 9]. For these patients, development of metastatic disease is the main cause of death.

Capecitabine is a non-cytotoxic fluoropyrimidine carbamate, which functions as an orally administered precursor of the cytotoxic agent 5-fluorouracil. Capecitabine is active as a single agent in colorectal cancer, and it is approved for the adjuvant and palliative treatment of patients with colorectal cancer [10]. Its value as a radiosensitizer in rectal cancer has been established by several phase II trials, with pathologic response rates that range from 7–38 % [11–15]. In a phase III non-inferiority trial, radiochemotherapy with capecitabine was shown to be non-inferior to 5-fluorouracil radiochemotherapy, with survival rates of 76 % at 5 years [16]. Taken together, these data and the more comfortable administration regimen of capecitabine compared to infusional 5-fluorouracil make it the preferential agent for the neoadjuvant treatment of patients with rectal cancer.

Colorectal cancer frequently overexpresses epidermal growth factor receptor (EGFR) [17]. Ligand binding to the extracellular portion of the receptor promotes homodimerization or heterodimerization and subsequent activation of the receptor. This leads to increased cell growth, proliferation, and mobility, decreased apoptosis, and stimulation of angiogenesis. Currently available drugs targeting the EGFR include monoclonal antibodies (e.g., cetuximab and panitumumab) and small molecule tyrosine kinase inhibitors (e.g., gefitinib, erlotinib, and lapatinib). In metastatic colorectal cancer, cetuximab and panitumumab were shown to be clinically effective [18–23]. Resistance to anti-EGFR antibodies may be mediated by HER-2, since the addition of anti-HER-2 targeting agents to cetuximab is able to overcome this resistance [24, 25]. These data support the development of therapeutic strategies targeting both EGFR and HER-2 in colorectal cancer. Additionally, targeting the EGFR pathway during neoadjuvant radiochemotherapy is associated with an increased number of cells in the G1 phase of the cell cycle (the most radiosensitive phase) and increased apoptosis, and prevents repair of DNA damage induced by radiation exposure, thus suggesting a possible synergistic effect of EGFR inhibition with radiation therapy [26, 27]. This strategy has been explored with cetuximab and gefitinib in combination with fluoropyrimidine-based radiochemotherapy in the phase I/II setting with disappointing results [28–30]. However, all these studies were conducted before the predictive role of RAS mutations in anti-EGFR treated patients was recognized; therefore, they may have been underpowered to detect a clinically relevant improvement for this therapeutic strategy.

Lapatinib is a small molecule dual tyrosine kinase inhibitor targeting both EGFR and HER-2. Preclinical studies have shown that lapatinib is active in colorectal cancer cell lines [31, 32], and its radiosensitizing properties have also been demonstrated in preclinical models [33, 34]. In treating metastatic colorectal cancer, lapatinib has been shown to be well tolerated, both as a single agent and in combination with chemotherapy, but with limited activity [35–38]. However, no population enrichment strategy based on tumor characteristics was implemented, and these trials may have been underpowered to identify any clinically relevant activity. Considering the clinical value of anti-EGFR therapy in RAS wild-type colorectal cancer [19–23, 39] and the theoretical advantage of anti-EGFR treatment during radiotherapy [26, 27] together with the data suggesting that dual inhibition of EGFR and HER-2 may be synergistic [31, 32], one can hypothesize that lapatinib is an ideal candidate for optimizing the neoadjuvant treatment of rectal cancer.

A randomized phase II trial with an adaptive Bayesian randomization design is proposed to assess the efficacy and safety of the tyrosine kinase inhibitor lapatinib combined with the fluoropyrimidine analog capecitabine as radiosensitizers in patients with clinical stage II/III resectable rectal cancer without activating RAS mutations.

## Methods/design

This single-center phase II trial is designed with an adaptive Bayesian randomization, which will allocate eligible patients to either lapatinib-capecitabine (arm A) or capecitabine (arm B) during standard radiation treatment for rectal cancer. The first 20 patients will be allocated at a 1:1 ratio. From that time point onward the randomization of a patient to either arm will be weighted by the updated estimate of the success probability in each arm, hence giving patients a higher chance of being allocated to the current most efficacious arm of the trial. The trial is designed to be stopped earlier if evidence of superiority of one arm over the other, futility, or unacceptable toxicity in arm A is identified.

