#### Determination of sample size

The trial’s objective is to show the superiority of the lapatinib and capecitabine combination (arm A) over the standard capecitabine (arm B). Thus, the null hypothesis is defined as H_0_: pB ≥ pA, where pA and pB are the probabilities of a pCR for arms A and B, respectively.

The expected sample size calculations were conducted in the context of a Bayesian adaptive randomization design, with stopping rules for early evidence of efficacy/futility and evidence of toxicity. These calculations are based on simulated trial results, which require presetting maximum and minimum total sample size, minimum number of patients fairly randomized to each arm, minimum probability of randomization for each arm, prior distributions for the treatment effect, and stopping rules for efficacy/futility.

We chose a maximum of 80 patients, based on the feasibility of patient’s accrual during the proposed study period. A minimum of 30 patients should be enrolled in the study before stopping the trial due to early evidence of efficacy/inefficacy. However, accrual may stop before the enrollment of 30 patients if there is evidence of toxicity, as defined below. The first 20 patients enrolled in the study will be fairly (non-adaptively) randomized to both arms. During the adaptive randomization phase, the minimum probability of randomization for each arm is set at 0.1.

For arm A, a non-informative prior for treatment effect, i.e., pA ~ Uniform (0,1), and for arm B, a moderate informative prior for treatment effect pB ~ Beta (1.2, 8.8) are used, as shown in Figs. 1 and 2, respectively.

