**Fig. 2 Fig2:**
[figure not shown]
Prior distribution for arm B

The trial will be stopped for efficacy if the probability of one arm being superior to the other is greater than 0.95 and for futility if the same probability is less than 0.05. Additionally, the trial stops for futility if the probability of arm A having an effect greater than 0.2 is less than 0.05.

Based on the previous setup, expected sample sizes were computed for three different scenarios, based on 10,000 simulations of trial results:I.pA = 0.30 and pB = 0.12II.pA = 0.25 and pB = 0.12III.pA = 0.12 and pB = 0.12

For scenario I, the expected sample size is 50 with 34 patients enrolled in arm A and 16 in arm B. The probability of choosing arm A as superior is 82 % (equivalent to the power concept in the frequentist framework), and the probability of early stop due to efficacy is 78 %. The expected trial length is 13 months. For scenario II, 56 patients are expected to enroll in the trial with 37 patients in arm A and 29 in arm B. The probability of identifying arm A as superior is 63 % (equivalent to the power concept in the frequentist framework), and the probability of early stop due to efficacy is 64 %. The expected trial length is 15 months. Finally, if no differences exist between the two arms (scenario III), the expected sample size is 60 (30 each arm). The probability of choosing one of the arms as superior is 12 % (equivalent to the probability of type I error in the frequentist framework). The expected trial length is 16 months.

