The proportion of pCR of each arm will be described and the efficacy of one arm over the other estimated by the posterior probability of superiority and its 95 % credible interval. The trial will be stopped for efficacy if the posterior probability of one arm being superior to the other is greater than 0.95 and for futility if the same probability is less than 0.05. Additionally, the trial stops for futility if the probability of arm A having an effect greater than 0.2 is less than 0.05. The posterior probability of superiority of arm A over arm B will be continuously calculated after the 30th patient outcome is known.

Adverse events will be described as absolute number of patients presenting any given adverse event during treatment, its proportion, and respective 95 % credible intervals. Data will also be summarized as total number of patients presenting at least one serious adverse event and its proportion. For analysis of serious adverse events, a summary posterior probability of a serious adverse event and its 95 % credible interval will be calculated. Patient accrual for arm A will be stopped for toxicity if there is evidence of a serious adverse event posterior probability (SAEPP) greater than 25 %. A conservative threshold of 0.5 will be used for the posterior probability of toxicity, meaning that the trial stops with moderate evidence (50 %) of SAEPP >25 % for arm A. A non-informative prior (Beta (1, 1)) for the proportion of toxic events was chosen. The boundary at each step is plotted in Fig. 3. Should this toxicity boundary be identified for arm A, accrual to the trial is interrupted for excess toxicity at a lapatinib dose level of 1250 mg/d. The trial will then restart with lapatinib at a dose level of 1000 mg/d in arm A, and the data from patients previously randomized to arm B will be used to adjust the prior distribution of pB necessary for random treatment allocation in the Bayesian framework previously defined. In this latter setting, should the toxicity boundary be crossed, accrual to the trial is stopped for toxicity and the combination of lapatinib with capecitabine as radiosensitizer will be considered too toxic for further study.

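### The adaptive allocation rule as described, read plainly, does not give the printed 34:16 split in scenario I; the formula actually simulated should be stated and the two made to agree

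*Protocol article*

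**What the plan says.** Only Methods/design describes how the adaptive allocation works. It starts with a run-in, "The first 20 patients will be allocated at a 1:1 ratio", after which randomization is "weighted by the updated estimate of the success probability in each arm". Success in this trial is pCR, the primary endpoint.

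Determination of sample size adds a constraint, "the minimum probability of randomization for each arm is set at 0.1", and the other inputs to the simulations: a uniform prior for arm A, "pB ~ Beta (1.2, 8.8)" for arm B, "We chose a maximum of 80 patients", and "A minimum of 30 patients should be enrolled in the study before stopping the trial" for efficacy or inefficacy. Randomization and stratification says only that after patient 20 the statistician supplies each result under the adaptive design.

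The same sample-size section reports the outcome of 10,000 simulations. For scenario I (pA 0.30, pB 0.12), 50 patients are expected, "with 34 patients enrolled in arm A and 16 in arm B", with 82% probability of choosing arm A. For scenario II (0.25 and 0.12), it prints a total of 56 with 37 in arm A and 29 in arm B, and 63%. For scenario III (0.12 in both), it prints 60 patients, 30 per arm, and a 12% probability of choosing either arm.

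The probability that one arm is superior appears only as a stopping and analysis quantity. It is nowhere named as the allocation weight.

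**The concern.** The allocation rule is the core of a response-adaptive design, and the expected split is one of its headline results. If the rule in the text and the rule behind the printed figures differ, the splits, power and type I error in Determination of sample size do not describe the trial that the text sets out.

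This is a practical matter. The article reports that the trial is recruiting, and after patient 20 the statistician issues allocations one by one. The Discussion also justifies the design partly by its protecting patients from a weakly performing arm, and how strongly it does so depends directly on how steep the allocation rule is.

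**Working it through.** **Inputs from the article.** Run-in of 20 patients at 1:1, taken as 10 per arm; priors Beta(1, 1) for arm A and Beta(1.2, 8.8) for arm B; floor 0.1; maximum 80; stopping from the 30th known outcome if the probability of superiority passes 0.95 or 0.05, or if Pr(pA > 0.2) < 0.05.

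**Assumptions.** The article does not give the number of outcomes still pending when a patient is allocated (the lag) or the spacing of looks used in its simulations. Both were varied.

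**Step 1: what the printed split requires.** In scenario I, arm A receives 34 − 10 = 24 of the 50 − 20 = 30 patients after the run-in, so its share there is 24/30 = 0.80. The overall share is 34/50 = 68%.

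**Step 2: hand check of the plain rule.** With weights at the true rates, arm A's share after the run-in is 0.30/(0.30 + 0.12) = 0.714. This gives 10 + 30 × 0.714 = 31.4 of 50, not 34.

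**Step 3: simulation with estimated rates.** The plain rule allocates to arm A with probability mA/(mA + mB), where mA = (1 + successes in A)/(2 + outcomes known in A) and mB = (1.2 + successes in B)/(10 + outcomes known in B), held within 0.1 to 0.9. The table uses a lag of 10 patients and a look after every outcome, which brings the total close to the stated 50. The plain and Pr(pA > pB) rows use 10,000 trials per scenario and the power-weight rows 3,000.

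| Rule | Scenario I, A:B | Total | Share to A after run-in (I) | Scenario II, A:B | Floor acts (I) |
|---|---|---|---|---|---|
| Plain ratio | 30.8:19.6 | 50.4 | 0.68 | 33.3:22.3 | under 1% |
| Squared rates | 33.6:16.7 | 50.3 | 23.6/30.3 = 0.78 | 36.5:19.0 | about 32% |
| Rates to power 2.5 | 34.5:16.0 | 50.5 | 24.5/30.5 = 0.80 | 37.2:18.3 | about 43% |
| Pr(pA > pB) | 34.8:15.9 | 50.7 | 24.8/30.7 = 0.81 | 37.8:18.2 | about 45–52% |
| Printed | 34:16 | 50 | 0.80 | 37:29, total 56 | not given |

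**Step 4: does the assumed lag drive this?** No. For the plain rule in scenario I, lags from 0 to 16 patients give an overall arm A share of 58–63% and a post-run-in share of 0.66–0.70. At lag 0 the split is 24.2:17.1 of 41.3. At lag 9 it is 30.1:19.3.

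**Step 5: error rates.** With 4 outcomes pending and looks every 10 outcomes:

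| | Printed | Plain ratio | Pr(pA > pB) |
|---|---|---|---|
| Choose A, scenario I | 82% | 84.3% | 82.2% |
| Choose A, scenario II | 63% | 69.2% | 65.5% |
| Choose either arm, scenario III | 12% | 14.4 + 0.8 = 15.2% | 11.8 + 0.5 = 12.3% |

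The two rules differ by 2.1, 3.7 and 2.9 points. With a look after every outcome and lag 9, the plain rule gives 87.5% in scenario I and 17.4% for choosing arm A in scenario III. Pr(pA > pB) gives 85.6% and 15.2%, so the differences are 1.9 and 2.2 points.

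**Step 6: scenarios II and III.** In scenario II, 37 + 29 = 66, not 56. A total of 56 would need 56 − 37 = 19 in arm B. Until that is corrected, arm A's share could be 37/56 = 66% or 37/66 = 56%, so scenario II cannot be used to identify the rule. In scenario III, 30:30 fits neither rule under the stated unequal priors: at lag 10 the plain ratio gives 34.7:28.1 and Pr(pA > pB) gives 36.6:26.1.

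**The case against.** The best defence is that the Methods/design sentence is an overview in a condensed article. It says allocation is weighted by the estimated success probability without saying that the weight is the simple ratio, and an exact formula may sit in the full protocol. Squared or similarly transformed success-probability weights also respect the wording, and they come close to the printed scenario I split. This largely stands. The missing formula is not itself the fault. The fault is that the one description given, taken at face value, disagrees with the printed result.

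Three stronger readings are tempting, and the article does not support them.

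- A reader might infer that allocation by Pr(pA > pB) was certainly the simulated rule. It fits, but so do power-transformed rates. With a look after every outcome it gives 85.6% in scenario I against the printed 82%, and it matches 82% and 12% only when looks are spaced.
- A reader might take the 0.1 floor as proof of that rule. The floor almost never acts under the plain ratio, but it is compatible with it, and it acts often under transformed weights too.
- A reader might infer a gap in the plan because Quantitative analysis says the posterior probability of superiority "will be continuously calculated after the 30th patient outcome is known". That sentence closes the account of the stopping rules and matches the 30-patient minimum. It governs when stopping is monitored and does not bar an earlier posterior for allocation.

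It is also fair to say that the effect on error rates is modest, and comparable with the misfit that remains under any rule with continuous looks.

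**Conclusion.** The mismatch holds. The plain reading of the stated rule gives about 30:19 of 50 in scenario I against the printed 34:16. That places roughly 3 to 4 more of 50 patients in arm B than the article reports. The conclusion does not depend on the assumed lag between 0 and 16 patients, and the hand calculation at the true rates (31.4 of 50) points the same way. Power and type I error differ by roughly 1 to 4 points between the plain rule and a steeper one, so the main effect is on the allocation that patients receive.

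The result rests on the stated priors, a 10:10 run-in, and reading the weight as the simple ratio of posterior mean pCR rates. Which rule was simulated remains unknown. The printed scenario I split shows only that it was probably steeper than the simple ratio. The point should be corrected, but it does not undermine the design.

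**What to change.** The trial statistician should state, in Methods/design and in Randomization and stratification, the exact allocation formula used in the 10,000 simulations, including any transformation and how the 0.1 floor is applied, and run that formula from patient 21. If the simulated rule is the one being run, this costs one or two sentences.

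If the plain ratio is the rule being run, the simulations need to be rerun and the expected splits, power and type I error in Determination of sample size restated for it. Stating the outcome lag and look spacing used would let a reader reproduce the figures.

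In either case, correct scenario II so that the arm counts and the total agree, and check scenario III's 30:30 against the simulation output.

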### Population and setting

The trial will be implemented at Instituto Português de Oncologia do Porto Francisco Gentil, EPE, where patients will be considered eligible for the trial based on the following criteria.

#### Inclusion criteria

Each patient must meet all of the following inclusion criteria to be enrolled in the study:Age of 18 years or aboveDiagnosis of adenocarcinoma of the rectum with the primary malignant lesion located between the dentate line up to 10 cm of the anal verge by endoscopic examinationAbsence of activation mutation in KRAS exons 2 (codons 12 and 13), 3 (codons 59 and 61), and 4 (codons 117 and 146) and NRAS exons 2 (codons 12 and 13), 3 (codons 59 and 61), and 4 (codons 117 and 146)Clinical stage II or III disease, according to American Joint Committee on Cancer Staging classification, 7th edition [40]. For clinical staging, the following procedures must have been conducted within 4 weeks of treatment allocation:Clinical history and physical examinationEndoscopic ultrasound of the primary lesionThoracic, abdominal, and pelvic computed tomographic (CT) scanClinically judged to be able to undergo curative resection of the rectal neoplasm despite preoperative radiochemotherapyClinically judged to be able to undergo pelvic radiation therapy to a total dose of 50.4 GyProvision of signed informed consent

#### Exclusion criteria

Patients meeting any of the following exclusion criteria are not to be enrolled in the study:Absence of baseline histological sample of the primary tumorPregnant or lactating womenUnwillingness or inability to comply with effective contraception, if the patient is fertile.Impaired renal function defined as creatinine clearance <60 mL/min according to the Cockcroft-Gault formulaImpaired hematological function as defined by any of the following on pretreatment evaluation:Hemoglobin concentration <10.0 g/dL,Absolute neutrophil count <1500/μLPlatelet count <100,000/μLImpaired hepatic function defined by any of the following on pretreatment evaluation:Serum level of aspartate aminotransferase >1.5 × ULN,Serum level of alanine aminotransferase >1.5 × ULN,Serum level of alkaline phosphatase >1.5 × ULN,International normalized ratio >1.5Serum concentration of total bilirubin >1.5 × ULNSymptomatic heart failure or a left ventricular ejection fraction (LVEF) below the institution’s lower limit of normality (LLN) as assessed through equilibrium radionuclide angiographyKnown intolerance to any of the study drugs.Known dihydropyrimidine dehydrogenase (DPD) deficiencyConcurrent treatment with CYP3A4 inducers (as detailed in the following section)Concurrent treatment with CYP3A4 inhibitors (as detailed in the following section)Likely inability to comply with the protocol or cooperate fully with the investigator and site personnelCurrent enrollment in another clinical trial.

